#### Evaluation of cost-effectiveness

A cost utility analysis will be conducted after 2 years of implementation to determine the financial impact of implementing the programme. The direct and indirect costs of implementing GLA:D® will be compared to its benefits. Using the 5-dimension EuroQol (EQ-5D) to measure health related QALYs, the raw and adjusted incremental cost-effectiveness ratio (ICER) will be calculated 1 year after the intervention. An exploration of healthcare utilisation pre- and post- participation in the GLA:D® programme will be conducted at each time-point (Additional file 3) and compared to national data from the TILDA study [45].

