**Methods:**

Using a type III hybrid implementation-effectiveness design, a participatory, dynamic and iterative process will be used to tailor and evaluate multi-level implementation strategies using the following stages: 1) Co-design the implementation strategies with key stakeholders using best evidence, a theory-driven implementation framework (Consolidated Framework for Implementation Research), local context and expert consensus; 2) Pilot and evaluate the implementation strategies by training physiotherapists to deliver the evidence-based Good Life with osteoArthritis Denmark (GLA:D®) education and exercise programme using the implementation strategies, and conduct a mixed-methods process evaluation; 3) Adapt the implementation strategies based on implementation process evaluation indicators from stage two. The adapted strategies will be used for scale-up and sustainability in subsequent GLA:D® Ireland training programmes that will be rolled out nationally. Evaluation of effectiveness on patient and cost outcomes will continue up to 12 months post-programme delivery, using an online patient registry and pre-post design.

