#### GLA:D® pilot programme delivery

GLA:D-trained physiotherapists (*n* = 8–10) will make use of existing or new referral sources to invite people with hip or knee OA to take part in the GLA:D® programme, as applicable for each setting. These sources include but are not restricted to clinic or orthopaedic waitlist, GP or other healthcare professional referral and self-referral. Eligible participants will have ‘joint problems from knee and/or hip that have resulted in contact with the health care system’. Exclusion criteria include non-OA cause of symptoms, e.g., tumour; inflammatory joint disease, or sequelae after hip fracture; other symptoms that are more pronounced than the OA problems, e.g., chronic, generalised pain, or fibromyalgia, acute knee trauma in the past 6 months or inability to understand the English language. The GLA:D® programme will comprise two to three education sessions and 12 (twice weekly) group neuromuscular exercise sessions as described in detail previously [15]. All group sessions will be supervised by a physiotherapist and can be delivered in a face-to-face or online format, as per clinician/patient preference and capability. Participants are encouraged to continue being physically active and to exercise, either with their physiotherapist or in their local community, to sustain the effects from the treatment in the long term.

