#### Evaluation of GLA:D® implementation

As established by Proctor and colleagues [41], a core set of implementation outcomes including: acceptability, adoption, appropriateness, cost, feasibility, fidelity, penetration and sustainability will be evaluated as outlined in Table 2*.* Implementation outcomes will be analysed descriptively using frequencies/proportions for categorical variables and means and standard deviations or medians and interquartile ranges for continuous variables.

**Table 2 Tab2:** Implementation outcomes and proposed method of collection

Outcome	Definition	Method of Collection (Level of analysis)
Acceptability	Satisfaction with various aspects of the programme	Survey on beliefs (Providers and patients); Survey on satisfaction at 3 months and 12 months post-programme (Providers and patients) Interview with providers: “Were you satisfied with the programme?” Interview with patients: “Were you satisfied with the programme?”
Adoption	Uptake and utilisation of the programme	Registry: Recording the number of referral sources, sites trained vs. sites implementing, trained physiotherapists and participant registrations from private and primary care settings (Providers and patients)
Appropriateness	Perceived fit, relevance, or compatibility of the programme for a given setting, provider, or consumer; and/or to address a particular issue or problem	Survey on beliefs (Providers and patients); Survey on satisfaction at 3 months post-programme (Providers and patients) Interview with providers: “How compatible is the GLA:D programme in your setting?” Interview with providers and patients: “Does the programme address a particular issue or problem?”
Cost	The financial impact of the implementation	Survey on barriers from WP1 (Providers and patients), Health utilisation and sick leave/medication use survey at 3 months and 12 months post-programme (Patients) Cost-effectiveness analysis Interview with providers and patients: “Have there been any cost implications?”
Feasibility	The extent to which the programme can be successfully used or carried out within a given setting	Collected with a survey at training course with strategies to overcome specific feasibility barriers discussed (Providers)
Fidelity	The degree to which the programme is implemented as it was prescribed in the original protocol	Interview with providers: “Did you make specific changes to the original programme? What did you change?”

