Dissemination activities arising from the results of this research will be co-planned and reviewed by the steering committee throughout the project. Annual reports, summarising evaluations on the effectiveness of the programme will be produced with accessible, lay terminology and infographics, and shared with clinicians and participants of the programme. Ensuring open access, these reports will also be available for free download on the GLA:D® Ireland website [47]. Sustainment of the GLA:D® Ireland initiative beyond the duration of project funding is one of the primary implementation indicators and will be addressed and tailored in implementation strategy design. The very nature of the implementation-effectiveness research design in this project will work to establish an evidence-based intervention within community healthcare settings. Nonetheless, it is critical that efforts to embed and sustain this initiative long-term are applied, through identification of the supports and processes required at micro, macro and meso levels. There is a clear need to identify and describe factors that affect sustainment outcomes in the field of implementation science, and a lack of evidence supporting discrete sustainment strategies for evidence-based interventions [48].

This research is limited by the pre-post design used to evaluate effectiveness of the intervention, without a comparative group. Since there are 100+ conclusive trials already completed in the area of exercise effectiveness for OA, the pre-post design was considered sufficient for the pragmatic monitoring of health outcomes in practice, alongside primary outcomes of implementation. This research may be subject to bias arising from the specific backgrounds and experiences of the researcher and steering committee members it is acknowledged, for example, that different group members may have prioritised or interpreted strategies and results in a different manner. Results of this research are also limited by the lack of available health administrative data to track healthcare usage in Ireland. However, using self-report, we can track use across private and public health services in this manner, that may not be feasible using health administrative data alone. This is important data to capture within a complex, two-tier system of care.

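### The planned incremental cost-effectiveness ratio has no comparator: in a single-arm pre-post registry, programme effect cannot be separated from regression to the mean or natural course

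*Protocol article*

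**What the plan says.** Under Evaluation of cost-effectiveness (Methods, Stage 3), the protocol article plans a cost utility analysis after two years of implementation. It states: "The direct and indirect costs of implementing GLA:D® will be compared to its benefits". QALYs are to come from the EQ-5D, and the planned result is worded as follows: "the raw and adjusted incremental cost-effectiveness ratio (ICER) will be calculated 1 year after the intervention". The section names no alternative strategy and does not define the adjustment. Healthcare use before and after participation is described separately, as an exploration, and is to be "compared to national data from the TILDA study".

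Two other places fix the design. The Methods part of the abstract says: "Evaluation of effectiveness on patient and cost outcomes will continue up to 12 months post-programme delivery, using an online patient registry and pre-post design". The Discussion says: "This research is limited by the pre-post design used to evaluate effectiveness of the intervention, without a comparative group". The Discussion then defends the design on the ground that many trials of exercise for osteoarthritis already exist, which makes pre-post data adequate for monitoring health outcomes in practice. It also says that the cost-effectiveness data will be used in making the funding case to the Department of Health and the Health Service Executive.

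**The concern.** An incremental ratio is a difference in cost divided by a difference in QALYs, each taken against something else the health service could do. The article commits to the ratio while describing a design that observes only one strategy. Whatever change occurs in EQ-5D between baseline and one year would be credited to the programme, including change that would have happened without it.

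The defence given in the Discussion does not reach this analysis. Trials showing that exercise works do not say how much of this cohort's EQ-5D change, or of its costs, is due to the programme.

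At stake is how the result is read. A funder who sees this ratio will take it as incremental to usual care in Ireland, and the planned data cannot support that reading.

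**Working it through.** **Inputs.** The article gives no EQ-5D standard deviation, expected gain, unit cost, threshold or ratio, so there is no figure to reproduce. Registry data are collected at baseline, 3 and 12 months (Evaluation of effectiveness).

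**Step 1: what the ratio needs.** ICER = (C1 − C0) / (Q1 − Q0), where 1 is the programme and 0 the alternative. The cohort supplies C1 and Q1. Possible sources for C0 and Q0 are:

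- *A concurrent group.* The Discussion says there is none.
- *Covariate adjustment.* Every registry patient receives the programme, so exposure does not vary within the cohort. Adjustment can change the case mix to which the estimate refers, but it cannot estimate outcomes without the programme.
- *TILDA.* It is used for healthcare utilisation only. No QALY change is taken from it, and it is not described as the comparator for the ratio.
- *Each patient's own baseline, carried forward.* This is the only reference left within the cohort.

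**Step 2: the QALY difference this implies.** Let d3 and d12 be the EQ-5D changes from baseline at 3 and 12 months. By the trapezoid rule over one year from baseline, less the baseline carried forward:

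Q1 − Q0 = 0.25 × d3/2 + 0.75 × (d3 + d12)/2 = 0.5 × d3 + 0.375 × d12.

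If the change is the same, d, at both visits, this is 0.875 × d. All of d is credited to the programme, whatever its cause.

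**Step 3: effect on the ratio (algebra only).** Suppose a fraction f of the observed QALY gain would have occurred anyway, and net cost is fixed and positive. Then true ICER = reported ICER / (1 − f).

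- f = 25%: 1/0.75 = 1.33 times the reported value.
- f = 50%: 1/0.50 = 2 times.
- f = 75%: 1/0.25 = 4 times.

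If patients would instead have worsened without the programme, f is negative and the reported ratio is too unfavourable. For example, f = −25% gives 1/1.25 = 0.8 times.

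**Step 4: can the size be pinned down?** This illustration uses assumed inputs that are not in the document. If the worst fraction of a normal population enters, regression to the mean in utility is i × SD × (1 − ρ), where i is the standardised mean shift at entry and ρ the correlation between baseline and follow-up.

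- Mild case (worst 90% enter, i = 0.195, SD 0.15, ρ = 0.8): 0.195 × 0.15 × 0.2 = 0.006 utility units, or about 0.005 QALY after multiplying by 0.875.
- Strong case (worst 50% enter, i = 0.798, SD 0.20, ρ = 0.6): 0.798 × 0.20 × 0.4 = 0.064 utility units, or about 0.056 QALY.

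With no programme effect at all, the apparent gain thus differs about elevenfold between the two cases (0.0638/0.0058). The article gives nothing with which to choose between them.

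**The case against.** The case on the other side has real force on several points.

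- *Recent contact.* A reader might infer that patients enter at a bad moment, just after seeking care. The eligibility wording is "joint problems from knee and/or hip that have resulted in contact with the health care system", with no time window, and entry may be from a waitlist or by self-referral. The Background notes that 45% of those waiting for an orthopaedic outpatient appointment had waited more than a year. Selection makes regression to the mean plausible, but the document does not establish it.
- *Overstated savings.* A reader might infer that a fall in healthcare use will be booked as a saving. The article keeps pre-post utilisation as a separate exploration and does not say that it enters the numerator. Bias could also run the other way: surgery among waitlisted patients could raise later costs, and worsening without treatment would make the carried-forward baseline too generous a reference.
- *Missing baseline utilisation.* Table 2 mentions the utilisation survey only at 3 and 12 months, which might suggest that no baseline value exists. But Evaluation of effectiveness says that the registry collects patient-reported data at baseline too, and the cost section speaks of use before participation. No gap is shown.
- *Unrestricted TILDA comparator.* The article does not say that all TILDA respondents will be used, and its Background cites TILDA figures that separate people with osteoarthritis from those without.
- *Limitation admitted and use qualified.* The absence of a comparative group is openly stated, implementation outcomes are primary, and the economic data are to be applied together with international evidence.
- *Condensed article.* A fuller plan may define the adjustment or name a reference strategy.

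All of these limit the point. None supplies an alternative strategy. The article itself fixes cost outcomes to a pre-post design, and its stated limitation and defence concern effectiveness and health outcomes, not the ratio.

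**Conclusion.** The point holds in this form: as stated, the planned ratio is not incremental to any alternative. With baseline as the only available reference, regression to the mean and natural course cannot be separated from programme effect.

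The multipliers of 1.33, 2 and 4 follow from assumed fractions of 25, 50 and 75% with net cost fixed and positive. They are not estimates for this study. The bias may be negligible or dominant, and its direction is not known. The documents do not support a claim that QALY gains or savings will certainly be overstated.

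This should be fixed, because it changes what can be taken to funders. It does not threaten the main objective, since the economic analysis is not a primary outcome.

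**What to change.** 1. Report the result as a before-after cost and QALY analysis, not as an incremental ratio against usual care. Alternatively, name an explicit external comparator that supplies both costs and QALYs.
2. State whether any pre-post change in healthcare use enters the numerator.
3. Pre-specify scenarios that attribute 25, 50, 75 and 100% of the EQ-5D change to the programme, and likewise of any cost change that is used. With programme cost P, change in other costs U, observed QALY gain G, and attributed shares a (QALYs) and b (costs), each scenario is (P + b × U) / (a × G).
4. Report the attribution at which the willingness-to-pay threshold is crossed. With net cost fixed and positive, this is the reported ratio divided by the threshold. For example, a ratio at half the threshold crosses it at 50% attribution.

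The cost is some wording and a few extra runs on data already planned, provided it is settled before the two-year analysis. Naming an external comparator would take more work. The downside is a more cautious headline for the funding case.

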## Discussion

With the IMPACT project, implementation of an evidence-based initiative for OA management in Ireland will be the result of comprehensive implementation strategy development using theory, best evidence, knowledge of the local context and needs of patients and clinicians and expert stakeholder consensus. This method will be used to systematically identify the multi-level barriers that exist and co-design solutions and strategies to overcome them.

Incorporating a participatory research approach and including end-users in the planning, design, implementation, and evaluation stages is seen as a critical approach to overcoming pragmatic barriers and ensuring the appropriate care is delivered to the patients who need it. Knock-on benefits of this research approach may come from seeding engaged networks of stakeholders that advocate for change in orthopaedic and musculoskeletal practice that result in benefits to the individual, healthcare system and society. While it was not deemed feasible in the planning stages to involve a policy-maker in all steering committee activities, opportunities to engage decision-makers and funders will be sought in a timely and strategic manner. Given OA is one of the most prevalent and disabling of chronic non-communicable disease, even small improvements in care that improve patient outcomes will incur savings. A budget impact analysis in Australia stated that only one in twelve GLA:D® recipients would need to avoid knee replacement surgery for the programme to generate savings [46]. In Demark, GLA:D® has shown cost-effectiveness at 1 year [16]. It is anticipated that similar future findings in Ireland will be leveraged to advocate for improved funding and access to physiotherapy-supervised exercise and education programmes for all patients with OA, in line with clinical guidelines. This aligns well with visioned plans to achieve universal healthcare in Ireland (Sláintecare) by 2028 [6], and to ensure all patients get access to the right care, in the right place, at the right time.

Implementation strategies are further operationalised by level i.e. micro, meso, macro. It is acknowledged that certain barriers may be non-modifiable within the scope and lifetime of this research study, particularly at a macro level. Nonetheless, strategies related to policy and engagement of stakeholders will work towards tailoring messages and driving change at these levels where appropriate. It is envisaged that patient outcomes and cost effectiveness data collected after 1 year of implementation will be used to leverage and advocate to Department of Health, the Health Service Executive and other relevant bodies to fund supervised exercise and education interventions for chronic musculoskeletal conditions. It will be important to apply this data alongside international evidence to help improve models of care and pathways for people with chronic hip and knee pain.

While local context is important to include with implementation efforts, this research has relevance beyond the specific setting in which it is being conducted. As with all intervention research, implementation strategies need to be fully and precisely described, in detail sufficient to enable measurement and ‘reproducibility’ of their components [24]. The details of the participatory health research process will be reported so that implementation projects work in other care settings, for other chronic conditions and other countries can be informed by lessons learned during that process. The use of theory in this study will also enhance the scope to accumulate knowledge about overcoming barriers to implementation [34]. Therefore, the strategies deemed to be effective will be published and shared widely for potential transfer and implementation in other healthcare settings, contexts and conditions.

Dissemination activities arising from the results of this research will be co-planned and reviewed by the steering committee throughout the project. Annual reports, summarising evaluations on the effectiveness of the programme will be produced with accessible, lay terminology and infographics, and shared with clinicians and participants of the programme. Ensuring open access, these reports will also be available for free download on the GLA:D® Ireland website [47]. Sustainment of the GLA:D® Ireland initiative beyond the duration of project funding is one of the primary implementation indicators and will be addressed and tailored in implementation strategy design. The very nature of the implementation-effectiveness research design in this project will work to establish an evidence-based intervention within community healthcare settings. Nonetheless, it is critical that efforts to embed and sustain this initiative long-term are applied, through identification of the supports and processes required at micro, macro and meso levels. There is a clear need to identify and describe factors that affect sustainment outcomes in the field of implementation science, and a lack of evidence supporting discrete sustainment strategies for evidence-based interventions [48].

This research is limited by the pre-post design used to evaluate effectiveness of the intervention, without a comparative group. Since there are 100+ conclusive trials already completed in the area of exercise effectiveness for OA, the pre-post design was considered sufficient for the pragmatic monitoring of health outcomes in practice, alongside primary outcomes of implementation. This research may be subject to bias arising from the specific backgrounds and experiences of the researcher and steering committee members it is acknowledged, for example, that different group members may have prioritised or interpreted strategies and results in a different manner. Results of this research are also limited by the lack of available health administrative data to track healthcare usage in Ireland. However, using self-report, we can track use across private and public health services in this manner, that may not be feasible using health administrative data alone. This is important data to capture within a complex, two-tier system of care.

The IMPACT project will use implementation science and participatory health research to address a gap in evidence-based management of OA across public and private healthcare settings in Ireland. This research has the potential to change practice and promote a policy of exercise and physical activity referral for chronic musculoskeletal disease that utilises community engagement effectively and enacts change ‘together’.

## Data Availability

Data sharing is not applicable to this protocol manuscript as no datasets were generated or analysed.

## Abbreviations

CFIR: Consolidated Framework for Implementation Research
ERIC: Expert Recommendations for Implementing Change
EQ-5D: 5-dimension EuroQol (EQ-5D)
GLA:D: Good Life with osteoArthritis from Denmark
GP: General Practitioner
ICER: Incremental cost-effectiveness ratio
IMPACT: Implementation of clinical guidelines for osteoarthritis together
OA: Osteoarthritis
QALY: Quality-adjusted life years
REC: Research ethics committee
RCT: Randomised controlled trials
SPIRIT: Standard Protocol Items: Recommendations for Interventional Trials
TILDA: The Irish Longitudinal Study on Ageing
